### Blinding

The researchers are in charge of sending randomization information and also receiving notices of the patient’s assignation. It is not practical to blind the researchers to treatment allocations. In addition, it is not possible to prevent participants from knowing if they have received EA treatment or standard wound care. However, it is feasible to blind outcome assessors and statisticians.

### Recruitment

Participants will be recruited via advertisements and posted notices. Advertisements will be broadcast on local television channels and also published in local newspapers. Posted notices will be put up on the notice board of the local hospital. A data compilation form including all variables of interest and all potential risks will be completed by the corresponding research center. The obtained information will be recorded on an electronic database for subsequent statistical analysis.

### Eligibility

#### Inclusion criteria

Participants will be included if they fulfill the following criteria: 1) pressure ulcers of grade II or III, according to EPUAP/NPUAP [12]; 2) duration of one or more pressure ulcers is greater than 3 months; and 3) aged 18 to 75 years old.

#### Exclusion criteria

Patients with any of the following conditions will be excluded: 1) undergoing any other therapies which might interfere with the ability to heal, such as corticosteroid therapy, radiation therapy, or chemotherapy for cancer; 2) severe diseases, such as severe liver, cardiac, kidney diseases, and relevant intensive complications, for reasons of safety as well as evaluation of pain intensity for patients with sensation loss; and 3) medical conditions for which EA is contraindicated [15], such as ventricular arrhythmia, atrial fibrillation, using cardiac pacemaker, history of deep radiation therapy within the local region, known deep venous thrombosis or thrombophlebitis, superficial metal ions or metal implants near the area, pregnancy, or active osteomyelitis.

### Intervention

The intervention was designed according to the record in the ancient book of *Yellow Emperor’s Inner Bible,* in Chapter *Lingshu*-*Guanzhen*[16] and according to the recent study of acupuncture as a treatment for pressure ulcers [17]. Standard wound care is a non-EA therapy option in this trial. The EA protocol was developed in consensus with acupuncturists and experts, who are good at acupuncture. In addition, this protocol is consistent with the Standards for Reporting Interventions in Clinical Trials of Acupuncture (STRICTA) guidelines for the performance of EA studies [18].

### Control group

Standard wound care will be used in the control group. In this study, standard wound care will include moving around and changing position, using mattresses and cushions, and a good diet. Keeping moving by moving around and changing position as much as possible should be restricted to less than 2 hours. Using mattresses and cushions can reduce the pressure on bony parts of the body. For patients with pressure ulcers of grade II, they should use a high specification foam mattress. As for pressure ulcers of grade III, patients should receive a more sophisticated mattress or overlay. A good diet of eating well and drinking enough water is very important. The healthcare professional will offer good dietary advice according to what is patients missing from the diet, their general health, and preferences.

### Treatment group

In addition to standard wound care, all participants in the treatment group will receive EA treatment. Hanyi needles (0.17 × 7 mm; Tianjin Medical Appliance Factory, Tianjin, China) and a Micro Plus transcutaneous electrical nerve stimulator (BioMedical Life Systems, Inc, Vista, CA, USA) will be used in the trial. Two needles will be punctured into the skin of the local wound. One needle will be inserted into the wound center with a 90° angle and connected with the negative pole, while the other needle will be punctured in the normal skin 0.5 cm away from the ulcer margin with a 45° angle and connected with the positive pole. Both needles will be applied without lifting, thrusting, or rotating. The electric stimulator will be turned on with 500 μA, 0.5 Hz, 30 minutes each time, for five sessions per week for 8 weeks.

### Outcome measures

#### Primary outcome

1) Wound surface area (WSA)

The pressure ulcer surface area will be measured by the use of acetate tracing and subsequent planimetric determination. Ulcer tracings will be accomplished by outlining the pressure ulcer circumference onto a transparent film applied directly over the wound. Each ulcer will be traced three times by two assessors, respectively, in order to improve the accuracy of the tracings. The ulcer surface area will be determined from the wound tracing using a planimeter (KP-21C) by a third assessor. All three assessors will be blinded as to the identity of the patient and to the treatment group assignment.

#### Secondary outcome

1) Visual analogue scale (VAS)

The pain intensity of pressure ulcers will be assessed using the 10 cm VAS (0, absence of pain; 10, worst pain imaginable) [19,20]. The VAS was selected as a secondary outcome measurement in order to evaluate the clinical severity and impact on activities of daily life in patients with pressure ulcers.

2) Proportion of ulcers healed within trial period (PUHTP)

The complete healed ulcers were defined as 100% epithelization or skin closure without drainage.

### Statistical methods

#### Sample size

This study is a pilot study for the evaluation of the efficacy of EA for patients with pressure ulcers and the feasibility of a large clinical trial. Because of the short duration, lasting 8 weeks, the desired sample size for this pilot study is 36 participants, with 18 participants in each group, assuming a dropout rate of 20%, which is the minimum sample size necessary to evaluate the effect of EA [21].

#### Analysis

Data will be analyzed by a statistician blinded to the allocation of groups. Statistical analyses will be conducted using the SPSS 17.0 statistical software packages (IBM, Armonk, NY, USA), and the levels of significance will be reported at *P* <0.05. The intention-to-treat (ITT) population will be defined as the participants who are randomized and received at least one treatment session. The data analysis of baseline characteristics, as well as the primary and secondary outcomes will be based on the ITT principle. Analysis of covariance will be conducted unless the adjustment for possible baseline incomparability is needed.

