**Comparison**					
Control group (n = 18)		40 sessions of standard wound care			

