**Safety**					
Adverse events		**×**	**×**	**×**	**×**

EA, electroacupuncture; PUHTP, proportion of ulcers healed within trial period; VAS, visual analogue scale; WSA, wound surface area; the symbol ‘x’ is used as a check mark.

This trial will include an 8-week treatment period and a 1-month follow-up period. After randomization, patients will receive a total of 40 session treatments over a period of 8 weeks. Outcome measurements will be assessed at baseline (1 week after participants are diagnosed with pressure ulcer), as well as at the end of the fourth week and 8 weeks after randomization, and 1 month after conclusion of the treatment phase. Patients will be informed that they may be assigned to an EA group, or control group.

This trial will be carried out according to the principles of the Declaration of Helsinki (version Seoul, 2008). This study protocol has been approved by the ethical review boards of the Second Affiliated Hospital of Heilongjiang University of Chinese Medicine, with permission number LLP2011012. All participants will be asked to provide written informed consent before enrollment, and will be given sufficient time to reach a decision to participate and sign the consent form.

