### Randomization

A randomization scheme will be performed at the Good Clinical Practice (GCP) Center of the Second Affiliated Hospital of Heilongjiang University of Chinese Medicine. This scheme will be used to assign participants to the EA group and control group in a 1:1 ratio. The randomization scheme will be generated by the central computer system. Two separate databases will be set up: the ‘participants’ database that includes basic participant information, such as name, contact details, and so on; and the ‘randomization’ database that holds data of patients registered on the trial and their allocation [14]. The practitioners participating in the study will not take part in the randomization process. Patients who meet the inclusion criteria and agree to provide written informed consent will be included in the study. The researcher will then contact the GCP center where the participant’s information is registered, and the randomization information of the patient’s assignation to one of the two study branches will be sent to the researcher by cell phone or via email. This procedure will ensure adequate randomization concealment, and is not influenced by the researcher taking part in this study.

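### The population called ITT drops randomised participants who never start treatment; in an open-label trial that exclusion may differ by arm and bias the comparison in either direction

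*Protocol article*

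**What the plan says.** The Analysis section of the protocol article defines the main population: "The intention-to-treat (ITT) population will be defined as the participants who are randomized and received at least one treatment session". It then says that the baseline characteristics "as well as the primary and secondary outcomes will be based on the ITT principle". No other section names a population that keeps all randomised participants.

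Four other places bear on how this rule would work.

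- **Sequence.** The Randomization section has the allocation sent to the researcher by phone or email once the participant is registered. The Design section, in the text after Table 1, puts treatment later: "After randomization, patients will receive a total of 40 session treatments over a period of 8 weeks".
- **Blinding.** On researchers: "It is not practical to blind the researchers to treatment allocations". On participants: "it is not possible to prevent participants from knowing if they have received EA treatment or standard wound care". Only those who measure and analyse are covered: "it is feasible to blind outcome assessors and statisticians".
- **Sessions in the control arm.** Table 1 gives this arm "40 sessions of standard wound care", so the rule of at least one session applies in form to both arms.
- **Content of a session.** Under Control group, standard care is repositioning, support surfaces and dietary advice. Under Treatment group, the EA arm gets the same care plus two needles, one of them in the middle of the wound, with electrical stimulation.

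**The concern.** Intention to treat means that everyone randomised is analysed in the arm assigned. The stated definition makes membership depend on something that happens after randomisation. It therefore describes a modified ITT population under the ITT name, and it is at odds with the principle cited for every outcome.

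Such a restriction is usually defended on the ground that failing to start cannot depend on the allocation. That defence normally rests on blinding, which is absent here for participants and researchers. The researcher knows the arm from randomisation, and the participant knows it by the first session at the latest. Starting EA and starting standard care are also different steps for the participant. The people removed before the first session may then differ between arms in number or in prognosis, and the remaining groups are no longer the groups that were randomised. The analysis of wound surface area, pain and healing would carry that difference while being reported as ITT.

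**Working it through.** **The plan's own figures.** The article gives no expected number of non-starters, so there is no stated figure to reproduce on this point. The inputs it does give are 18 participants per arm, 36 in total, and an assumed dropout of 20% (Sample size). The basis of 36 cannot be checked, because no effect size, SD or power is stated. The dropout step alone is compatible with 14 evaluable per arm: 14 / (1 − 0.20) = 17.5, rounded up to 18. The present point does not depend on it.

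**Logic of the definition.** With k non-starters in one arm, the stated set holds 36 − k participants, whereas a set of all randomised participants holds 36. Each exclusion removes 1/18 = 5.6% of an arm. If k = 0 the two sets are the same.

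**Illustrative size.** Assumptions, none of them from the documents: all k non-starters are in one arm, their mean outcome differs from that of the starters by d SD, there is no true treatment effect, the SD is 1 in both arms, and the test is a two-sided normal-approximation test at 0.05.

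- Shift of the arm mean caused by the exclusion = (k/18) × d.
- Standard error of the difference = √(1/(18 − k) + 1/18).

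| k | SE (SD units) | Shift, d = 0.5 | Type I error, d = 0.5 | Shift, d = 1.0 | Type I error, d = 1.0 |
|---|---|---|---|---|---|
| 1 | 0.338 | 0.028 | 0.051 | 0.056 | 0.053 |
| 2 | 0.344 | 0.056 | 0.053 | 0.111 | 0.062 |
| 3 | 0.350 | 0.083 | 0.057 | 0.167 | 0.076 |

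The largest case is 0.167 / 0.350 = 0.48, about half a standard error. The type I error is the same whichever sign d has. The sign only decides which arm gains. Equal numbers of non-starters in both arms with the same d would cancel in the difference.

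**Same point for healing.** Assume one ulcer per participant and 6 healed among 18 randomised, a base rate chosen only for illustration (33.3%). If the excluded participants were unhealed, the rate becomes 6/16 = 37.5% (two excluded) or 6/15 = 40% (three). If they were healed, it becomes (6 − 2)/16 = 25% or (6 − 3)/15 = 20%. The treatment effect is unchanged in each case. Only the denominator rule has moved the result.

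**The case against.** The other side has a good deal to say.

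- **Consent comes first.** The Design section says that participants are told they may be assigned to either group and have time to decide before enrolment. Many who would refuse needling will decline before randomisation. This stands, and it makes a large number of EA non-starters less likely.
- **The window is short.** Table 1 places randomisation and the start of treatment in the same week-0 column, and anyone who stops after one session stays in the set. This also stands. If the 20% dropout covers the whole study, it is 0.20 × 18 = 3.6 per arm, so three non-starters would use most of it before the first session.
- **It is a pilot, and withdrawals are documented.** Quality control requires drop-outs and their reasons to be recorded, so exclusions could be seen afterwards. That limits the harm but does not correct the definition. The stated primary objective is efficacy, and the significance level is set at 0.05.

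A reader might go further and infer that exclusions will fall mainly on the EA arm and will favour EA. The documents do not support that. The rule is worded alike for both arms. Recruitment is by advertisement, so participants disappointed at being controls could also leave once they know their arm. Nothing indicates whether non-starters would do worse or better than starters.

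None of this answers the central point. The definition is stated in the article, applied to all outcomes, and is not ITT. It is not a detail that an unseen analysis plan would merely fill in.

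**Conclusion.** The definition is wrong as written. It gives the ITT name to a modified population and opens the primary comparison to exclusions that may depend on a known allocation. Blinding the assessors and statisticians does not help, because the exclusion happens before they are involved.

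The size is unknown and may be nil. Under the assumptions above, 1 to 3 non-starters in one arm shift its mean by about 0.03 to 0.17 SD and move the two-sided type I error from 0.05 to between 0.051 and 0.076. With one or two non-starters it stays at or below 0.062. These figures illustrate scale only and do not predict direction. Because the effect cannot be known beforehand and the correction is cheap, this should be fixed before analysis. The evidence does not make it a fatal flaw.

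**What to change.** 1. Define the ITT population as all randomised participants, analysed in the arm assigned, whether or not any session was received, and use it for baseline, primary and secondary outcomes.
2. Seek wound surface area, pain and healing status at 4 weeks, 8 weeks and follow-up on participants who never start. The article does not say that these visits lapse for them, so this makes explicit what the definition needs. Table 1 already places the baseline outcomes at week 0, the same visit as randomisation, so baseline values may well be available.
3. Rename the set that requires at least one session as modified ITT, and use it only as a sensitivity analysis.
4. Report the number of non-starters by arm, with reasons. This also serves the trial's feasibility aim.

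The cost is a change of wording and a few outcome visits that are already in the schedule. The article reports that the trial is still recruiting, so the change can be made before the data are analysed.

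### The covariate rule is worded backwards: read literally, it withdraws ANCOVA when baseline adjustment is needed, and names no analysis in its place

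*Protocol article*

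**What the plan says.** The Analysis section has one sentence on how the groups will be compared: "Analysis of covariance will be conducted unless the adjustment for possible baseline incomparability is needed". The sentence before it applies the intention-to-treat principle to baseline characteristics and to the primary and secondary outcomes together, so the rule is not tied to one outcome. The article does not say which analysis replaces ANCOVA, which covariates are meant, or how the need for adjustment is judged. No other section restates or corrects the rule.

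The surrounding facts are these:

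- **Primary outcome.** WSA is continuous: "The pressure ulcer surface area will be measured by the use of acetate tracing and subsequent planimetric determination". Table 1 schedules both WSA and pain VAS at week 0, so a baseline value exists for each.
- **Size.** "the desired sample size for this pilot study is 36 participants, with 18 participants in each group", "assuming a dropout rate of 20" per cent.
- **Allocation.** The scheme will "assign participants to the EA group and control group in a 1:1 ratio". No stratification on wound size is described.
- **Significance level.** 0.05; the article does not say one- or two-sided.

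**The concern.** ANCOVA on the baseline value is the usual way to deal with a chance difference in starting wound size. A rule that keeps ANCOVA unless such adjustment is needed has the logic reversed. If ANCOVA gave way to an unadjusted comparison, a chance baseline gap would pass into the estimated effect on WSA in proportion to the correlation between baseline and follow-up.

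Replacing *unless* by *if* does not fully cure this. The analysis would still be chosen after looking at the baseline data, by a criterion the article does not state. In most trials the precision available from week-0 WSA would be thrown away.

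An unseen analysis plan does not excuse the sentence. The fault lies in what the article states, and a plan with the right rule would contradict it.

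**Working it through.** **The plan's own figure.** The total of 36 cannot be reproduced, because no effect size, SD or power is given. Only the dropout step can be checked: 18 × 0.80 = 14.4, so about 14 evaluable per arm, and 14 / 0.80 = 17.5, rounded up to 18. The calculations therefore use 14 and 18 per arm.

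**Assumptions not in the document.** Normal outcomes with equal SDs; two-sided 0.05; baseline/follow-up correlation r from 0.3 to 0.85; need for adjustment judged by a baseline t test at p<0.05, 0.10 or 0.20; an unadjusted t test wherever ANCOVA is not used.

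**How often a sizeable gap arises.** The SE of the baseline mean difference, in SD units, is √(2/n).
- n = 18: √(2/18) = 0.333; 0.5/0.333 = 1.50; P(gap ≥ 0.5 SD) = 2(1 − Φ(1.50)) = 0.134.
- n = 14: √(2/14) = 0.378; 0.5/0.378 = 1.32; P = 0.186.

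**Bias given a gap.** Conditional on the observed gap, the unadjusted difference is off by r × gap. A 0.5 SD gap gives 0.15, 0.25 or 0.35 SD for r = 0.3, 0.5 or 0.7. Among trials flagged at p<0.05 with 14 per arm the mean gap is about 0.85 SD, so at r = 0.7 the bias is 0.7 × 0.85 = 0.60 SD.

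**Simulation, 14 per arm** (200,000 trials per setting). Ranges run over the three flagging thresholds. The two columns for flagged trials use p<0.05.

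| r | Bias in flagged trials, unadjusted (SD) | Type I error in flagged trials, unadjusted | Overall type I error, literal rule | Overall type I error, *if* reading |
|---|---|---|---|---|
| 0.3 | 0.24 | 9% | 5.2–5.4% | 4.6–4.8% |
| 0.5 | 0.43 | 17% | 5.6–6.1% | 3.8–4.3% |
| 0.7 | 0.60 | 32% | 6.3–7.4% | 2.7–3.8% |
| 0.85 | 0.72 | 49% | 7.2–8.4% | 1.7–2.8% |

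ANCOVA in every trial holds about 5%, overall and in flagged trials. With 18 per arm the pattern is the same: bias in flagged trials is 0.23 to 0.64 SD, and the *if* reading goes down to 1.6%. Separate runs moved the flagged-trial error by about one percentage point and the overall error by about 0.1 point, so the overall ranges are quoted as 5.2% to 8.5% and 1.6% to 4.9%.

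**Cross-check at r = 0.7, flag at p<0.05.** The literal rule mixes ANCOVA in 95% of trials with the unadjusted test in 5%: 0.95 × 5% + 0.05 × 32% = 6.35%, against 6.3% simulated. The *if* reading falls below 5% because the unadjusted test is conservative in balanced trials, where it still charges for baseline variation that is absent.

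**Power for a true 0.8 SD effect, 14 per arm**

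| r | ANCOVA always | Unadjusted always | *if* reading |
|---|---|---|---|
| 0.3 | 55% | 53% | 53% |
| 0.5 | 63% | 53% | 53–55% |
| 0.7 | 80% | 53% | 54–58% |
| 0.85 | 97% | 53% | 55–62% |

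**The case against.** The best defence is that *unless* is a slip for *if* or *when*, so the large conditional errors describe a rule that nobody intended. That is probably true of the intent. It does not rescue the text: the sentence is uncorrected, and the intended version would still let the data choose the analysis. On that version, though, the type I error is conservative rather than inflated.

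A reader might infer that the primary comparison is planned as unadjusted and will be biased. The article does not support that. It names no fallback, and a change score or another adjusted model is not ruled out. Even an unadjusted difference is unbiased averaged over all randomizations (about 0.001 SD in simulation). The bias exists only given an imbalance, which a p<0.05 flag picks up in about 5% of trials. The literal rule also keeps ANCOVA in the other 95%: at that threshold, with 14 per arm and r = 0.7, its power is about 79% against 80% for ANCOVA always.

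A reader might also infer that a material imbalance in wound size is likely here. A gap of 0.5 SD or more arises in about 13% of trials with 18 per arm and 19% with 14. That is plausible, but not likely.

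Nor can one say without qualification that adjusting only on imbalance costs much power. The cost is trivial at r = 0.3 and large at r = 0.85, and the article gives no value of r.

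Finally, the trial is described as a pilot, which lowers the stakes. Its stated primary objective is nevertheless efficacy, so the primary comparison should still be fixed in advance.

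**Conclusion.** The sentence is wrong as written and needs correcting. Its literal meaning reverses the purpose of ANCOVA, and its likely intended meaning leaves a data-dependent choice of analysis.

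The overall effect is modest and the conditional effect can be large. If the fallback is an unadjusted test, overall type I error is about 5.2% to 8.5%. In the roughly 5% of trials flagged at p<0.05 it is about 9% to 49%, with bias of about 0.23 to 0.72 SD towards the imbalance. On the *if* reading, type I error is about 1.6% to 4.9%, and power for 0.8 SD with 14 per arm is about 53% to 62%, against 55%, 63%, 80% or 97% with ANCOVA always, for r = 0.3, 0.5, 0.7 or 0.85.

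The reversed wording is certain. The sizes rest on the assumed fallback, flagging rule, correlation and normality. Wound area is bounded at zero and healed ulcers would score zero, so the true figures may differ.

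**What to change.** Replace the sentence with:

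> WSA will be compared between groups by ANCOVA with week-0 WSA as covariate, in all participants, regardless of any observed baseline difference.

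Use the same form for VAS, with baseline VAS as covariate. The sentence should be read with the time point chosen for the primary comparison, since WSA is measured at 4 weeks, 8 weeks and one month after treatment; this correction does not settle that choice. Ulcer grade may be added as a factor, but that is optional and was not examined here.

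The cost is one sentence, agreed before unblinding. Both baseline values are already scheduled in Table 1. The one price is a degree of freedom for the covariate, and at the lowest correlation examined (r = 0.3) ANCOVA still had slightly more power than the unadjusted test.
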